## 4.2 Rationale for Trial Design

Randomised double-blind placebo-controlled studies are considered the gold standard.

The study is randomised so that unknown or unmeasurable variables do not lead to biased or incorrect results.

The study is double-blind to prevent researchers from treating the groups differently. This approach avoids bias in confirming the hypothesis and interpreting results. It also prevents a disproportionately large placebo effect.

The study is placebo-controlled so that psychosomatic effects do not influence the study outcome.

Studies investigating the effect of olive extract or combination preparations containing olive extract on blood pressure and cholesterol have observed changes in these parameters after an 8-week intervention [10,11]. The intervention in this study lasts 8 weeks but may be extended to 9 weeks for practical reasons.

The primary objective of this study is to assess the influence of the preparation on blood pressure. For this reason, both systolic and diastolic blood pressure will be measured during the screening visit, after 4 weeks, and at the final visit.

To observe changes in oxidative stress markers, MDA, oxLDL, and GSH will be measured in plasma samples collected during the screening and final visits.

At the final visit, participants will be asked about any experienced side effects to evaluate product tolerance.

Total cholesterol, HDL, LDL, non-HDL, remnant cholesterol, triglycerides, apolipoprotein A1, apolipoprotein B, and lipoprotein(a) will describe the participant's lipid profile. These parameters will be determined at the start and end of the study.

Additionally, BMI, waist circumference, fasting glucose, haemoglobin A1c, insulin, and fasting C-peptide will be monitored because abdominal obesity and glucose intolerance are components of MetS.

Haemoglobin, creatinine, ultra-sensitive C-reactive protein, and homocysteine will also be monitored as these parameters are linked to cardiovascular risk.

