| Week 0                                                                                                                                                                                                                                                                                                                                                                                 | Week 4 after start treatment                                                                                | Week 8 – 9 after start treatment                                                                                                                                                                                                                                                                                                                  |
| 
 
Review and signing of Informed Consent Form
 
Complete contact form
 
Blood pressure measurement
 
Check inclusion and exclusion criteria
 
Complete Food Frequency Questionnaire
 
Complete start questionnaire
 
Measure weight, height, and waist circumference
 
Blood sampling
 
 | 
 
Blood pressure measurement
 
Adverse event inquiry
 
 | 
 
Blood pressure measurement
 
Complete Food Frequency Questionnaire
 
Complete end questionnaire
 
Measure weight and waist circumference
 
Unblinding
 
Provide book voucher and Tensiofytol® packaging if the participant received placebo during the study
 
 |

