#### 3.2 Endpoints

|                    | Objective                                              | Endpoint                                                                                                                               |
|--------------------|--------------------------------------------------------|----------------------------------------------------------------------------------------------------------------------------------------|
| Primary     | Decrease in blood pressure                             | Systolic blood pressure*                                                                                                               |
| Secondary   | Decrease in blood pressure                             | Systolic blood pressure after 4 weeks*                                                                                                 |
|                    | Decrease in blood pressure                             | Diastolic blood pressure*                                                                                                              |
|                    | Change in markers of oxidative stress                  | oxLDL*, MDA*, GSH*                                                                                                                     |
|                    | Change in lipid profile                                | Total cholesterol*, HDL*, LDL*, non-HDL*, Remnant cholesterol*, Triglycerides*, Apolipoprotein A1*, Apolipoprotein B*, Lipoprotein(a)* |
|                    | Evaluation of side effects                             | Side effects                                                                                                                           |
| Exploratory | Change in parameters linked to metabolic syndrome.     | Fasted glucose*, Hemoglobin A1c*, fasted insulin*, fasted C-peptide*                                                                   |
|                    | Change in parameters linked to metabolic syndrome.     | BMI* en waist circumference*                                                                                                           |
|                    | Change in parameters linked to cardiovascular diseases | Hemoglobin*, Creatinine*, CRP-US*, Homocysteine*                                                                                       |

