#### **7.1.1 Criteria for Permanent Discontinuation of Trial Intervention**

The treatment will be stopped if the participant meets any exclusion criteria during the study, such as starting smoking or changing their diet.

The treatment may also be stopped if the participant wishes, experiences discomfort from the treatment, or for any other reason.

The participant must return any remaining study product capsules.

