#### **7.1.2 Temporary Discontinuation or Interruption of Trial Intervention**

Temporary discontinuation of treatment is not allowed. Stopping the treatment will result in exclusion from the study.

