### 8.5.2 Time Period and Frequency for Collecting AE and SAE Information

Throughout the study, from the start of intake until the final visit, AE and SAE data can be collected. After the study ends, participants will not be actively asked whether AEs or SAEs occurred.

During the final visit, a questionnaire will be completed asking about side effects or discomfort.

At the intermediate blood pressure measurement, there is an in-person contact moment where participants are asked how they tolerate the study product.

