### 8.5.3 Identifying and Recording of AEs and SAEs

Participants have the contact details of the investigators and the principal investigator – medical monitor. AEs and SAEs can be reported this way. In case of an SAE, investigators and the medical monitor must be notified immediately.

At in-person visits, participants are asked how they tolerate the study product. Any comments are noted.

During the final visit, participants complete the final questionnaire, which asks about side effects and their severity. If possible, a start and end date for each complaint will be specified.

AEs and SAEs are recorded in the “Adverse Events / Serious Adverse Events” register. For each event, a description, start and end date, outcome, severity, and actions taken are documented.

It is then assessed whether the AE meets the criteria for SAE and whether it may be related to the treatment.

This assessment is done in consultation with the principal investigator – medical monitor.

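### No side-effect questions are planned when a participant stops or withdraws, although discomfort is a named reason for stopping and side effects are a secondary endpoint

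*Protocol*

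**What the plan says.** The endpoint table (Protocol 3.2) lists "Evaluation of side effects" among the secondary objectives. The endpoint is simply side effects, with no data source named.

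Collection is described in several places:

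- Section 4.2 mentions the final visit only: "At the final visit, participants will be asked about any experienced side effects to evaluate product tolerance".
- Section 8.5.2 places the questionnaire there as well: "During the final visit, a questionnaire will be completed asking about side effects or discomfort". Section 8.5.3 gives its content: "During the final visit, participants complete the final questionnaire, which asks about side effects and their severity". Dates are added where possible.
- The Schedule of Activities (1.3) also lists, at week 4, "Adverse event inquiry". Section 8.5.2 describes that contact: "At the intermediate blood pressure measurement, there is an in-person contact moment where participants are asked how they tolerate the study product".
- Section 8.5.3 lets participants report events to the team at any time. It sets up a register that records, for each event, a description, dates, outcome, severity and actions taken.

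On leaving, section 7.1.1 states: "The treatment may also be stopped if the participant wishes, experiences discomfort from the treatment, or for any other reason". The Risk Summary (2.2) also gives discomfort from the supplement as its example of why someone might stop. Section 7.1.2 adds: "Stopping the treatment will result in exclusion from the study". Sections 7.1.1 and 7.2 require a leaver to return unused product and nothing else. Section 8.1 lists three visits, none of them for early termination. Section 8.5.4 says there is no active questioning about adverse events once the study is over.

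**The concern.** Whether a participant is asked about side effects depends on whether they stay, and the Protocol itself expects some to leave because of side effects. The people least likely to be asked may be those who tolerated the product worst. If the olive extract causes complaints that make people stop, and placebo does not, the under-count falls mainly on the active arm and the comparison of tolerance is flattered. With 28 participants per arm, one or two unasked stoppers are enough to move a side-effect rate visibly.

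This is a matter of data collection. An analysis plan can define populations and sources, but it cannot recover answers that were never requested. The point does not concern the blood-pressure comparison.

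**Working it through.** **Who is asked what.** Putting sections 1.3, 7.1.1, 7.1.2, 7.2, 8.1, 8.5.2 and 8.5.3 together:

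| Course of participant | Week 4 inquiry | Final questionnaire | Asked on stopping | Own report to register |
|---|---|---|---|---|
| Completes | yes | yes | not applicable | possible |
| Stops before week 4 | no | no | not planned | possible |
| Stops between week 4 and weeks 8–9 | yes, for complaints up to then | no | not planned | possible |

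That a stopper misses the final visit is inferred from the exclusion sentence in 7.1.2 and the three-visit list in 8.1. It is the natural reading, and nothing in the Protocol provides otherwise. The register is a place to record events. Apart from the two scheduled contacts, it is filled by what participants choose to report. Someone who stops before week 4 is never actively asked, and someone who stops later is not asked about a complaint that arose after week 4.

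**How many leavers the plan allows for.** The only related figure in the Protocol is the dropout allowance in section 9.2. A two-sample t-test with difference 10.4 mmHg, SD 11.4 mmHg, two-sided alpha 0.025 and 80% power gives 25 per group (power 0.816 at 25), which reproduces the stated number. Then 25 / (1 − 0.10) = 27.8, rounded up to 28, also as stated. The allowance is 28 − 25 = 3 per arm; equivalently 0.10 × 28 = 2.8 per arm, or 0.10 × 56 = 5.6 in total. It covers dropout for any reason. The Protocol does not say how many would stop for discomfort.

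**Illustration of scale, with assumed counts.** In one arm of 28, suppose that 2 completers report a side effect and d participants stop for discomfort.

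- Everyone treated, with every stop for discomfort counted: (2 + d) / 28.
- Final questionnaire alone: 2 / (28 − d).

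| d | Everyone counted | Questionnaire alone | Gap (percentage points) |
|---|---|---|---|
| 1 | 3/28 = 10.7% | 2/27 = 7.4% | 3.3 |
| 2 | 4/28 = 14.3% | 2/26 = 7.7% | 6.6 |
| 3 | 5/28 = 17.9% | 2/25 = 8.0% | 9.9 |

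Under these assumed counts, the gap is the extreme case, in which neither the week 4 inquiry nor the register captures any stopper. If those routes capture all of them and the register is used for the endpoint, the gap is zero. The row d = 3 is high, because it assigns the whole all-cause allowance to discomfort. Using everyone treated as the denominator does not help by itself: uncaptured stoppers then count as free of side effects, giving 2/28 = 7.1%.

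**The case against.** The strongest reply is that the Protocol has more than one source on tolerance. There is a scheduled week 4 inquiry, an open reporting route throughout intake, and a register with more fields than the questionnaire. A symptom that makes someone stop meets the adverse-event definition in 8.5.1 and can be registered once the team knows of it. Returning capsules implies some contact. Section 10.3 allows data gathered during participation to be used after someone leaves. Section 4.2 is a short rationale, while section 8.5 sets the procedure. The endpoint table restricts the endpoint neither to the questionnaire nor to completers, and the choice of source and analysis population may properly sit in the analysis plan.

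Most of this stands. A reader might infer that the final questionnaire is the only structured instrument, so that the endpoint necessarily omits those who tolerated the product worst. The documents do not support that, because the register is structured and can hold their events. A reader might also treat all three planned leavers per arm as intolerant and conclude that the reported rate would be roughly halved. That does not follow either: the allowance is for all causes, and section 7.3 expects few to leave.

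What the reply does not answer is the difference between being asked and having to volunteer. None of these routes prescribes a side-effect question, or a recorded reason, at the moment of stopping. Capsule return is an opportunity to ask, but the Protocol does not use it.

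**Conclusion.** The point holds in a limited form. The Protocol plans no solicited side-effect collection when a participant stops or withdraws, so completers are questioned systematically while those who stop for discomfort depend partly or wholly on volunteering. This non-collection is related to the outcome and can lead to under-counting of the side effects that cause stopping.

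The size cannot be derived from the documents. It depends on how many stop for discomfort, how many of those report it themselves, and whether the endpoint uses the register. The illustration of 3.3 to 9.9 percentage points in one arm rests on assumed counts with no capture by other routes, so it shows scale only and is not an estimate.

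Section 4.2 is also narrower than 1.3, 8.5.2 and 8.5.3, and these should be reconciled. The change is cheap and worth making. It does not affect the primary endpoint.

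**What to change.** - In sections 7.1.1, 7.2 and 8.5.2, state that a participant who stops or withdraws is offered the existing side-effect questions from the final questionnaire, by telephone or post, if they agree. Record the reason for stopping in the adverse-event register.
- State that side effects and stops for discomfort are reported by arm for everyone who took the product, drawing on the final questionnaire, the week 4 inquiry and the register.
- Bring section 4.2 into line with sections 1.3, 8.5.2 and 8.5.3, so that all describe the same collection points.

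The cost is one short call or mailed form per leaver, for about 3 per arm if the dropout allowance is met, using questions that already exist. Reported tolerance may look slightly less favourable. No treatment or stopping rule changes.

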### 4.2.1 Rationale for placebo

The chosen placebo will have the same appearance and form as the study product. This way, participants will not know whether they are taking the placebo or the olive extract.

### 4.3 Access to Trial Intervention After End of Trial

At the final visit, the participant must return any remaining study product to the researcher. The study product, Tensiofytol®, is available over the counter. Participants may purchase the product themselves if they wish. If, after unblinding, the participant is found to have taken the placebo, they will receive one package of 112 capsules (for 8 weeks) free of charge.

### 4.4 Start and End of Trial

|                         |                                                                           |
|-------------------------|---------------------------------------------------------------------------|
| Study Preparation:      | January – April 2021                                                      |
| Start of Recruitment:   | June 2021                                                                 |
| End of Recruitment:     | When all participants have been enrolled (February 2024)                  |
| Analysis and Reporting: | 2 months after the final visit of the last participant (April – May 2024) |

## 5. Trial Population

### 5.1 Selection of Trial Population

The study investigates the effect of Tensiofytol® in individuals with elevated systolic blood pressure ( $\geq 130$  mmHg).

Participants are aged  $\geq 18$  years and  $\leq 77$  years.

### 5.2 Rationale for Trial Population

Because the reduction in systolic blood pressure is the primary endpoint of this study, individuals with elevated systolic blood pressure were chosen as the study population. The product is currently commercially available as a supplement that helps maintain balanced blood pressure.

Participants are adults who are capable of providing informed consent for participation.

Individuals who do not meet these criteria may not be included in the study by exemption from these requirements.

### 5.3 Inclusion Criteria

To participate in this study, the potential participant must meet the following criterion:

1. An average systolic blood pressure  $\geq 130$  mmHg

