## 4. Trial Design

### 4.1 Description of Trial Design

This is a randomised, placebo-controlled, double-blind study. It includes 56 participants, equally divided into 2 groups (28 participants per group). One group will receive Tensiofytol®, and the other will receive a placebo.

Participation in this study will take a maximum of 10 weeks. The potential participant will be invited for a screening visit. If eligible, the participant will be randomised. The study product will then be delivered to the participant as soon as possible. Intake of the study product must start no later than 1 week after the screening visit. The participant must then take the study product or placebo daily. An interim blood pressure measurement will take place 4 weeks after starting intake. The final visit will be scheduled 8 to a maximum of 9 weeks after starting intake. After the final visit, the participant will be unblinded, marking the end of participation.

Participants will be stratified by sex and then randomised into 2 groups. This will occur 1 to 2 days after the screening visit, once all results are available.

This study is double-blind. The investigators do not know which group the participant is assigned to. The participant will be informed of the treatment they received during the final visit, after all data have been collected. The randomisation list and unblinding at the final visit will be handled by a separate study staff member responsible solely for these tasks.

This is a single-centre study. Participants will be enrolled by researchers from the NatuRAPT research group.

Statistical analysis will be performed after all data from all participants have been collected. No interim analysis is planned.

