### 5.4 Exclusion Criteria

Individuals meeting any of the following criteria will be excluded from participation in this study:

- Age  $< 18$  years or  $> 78$  years
- Smoking
- Triglyceride level  $> 400$  mg/dL
- More than 14 alcoholic drinks per week
- Chronic illness (e.g., diabetes, atherosclerosis, rheumatoid arthritis, ...)
- Acute inflammation
- Pregnancy or intention to become pregnant during the study period
- Breastfeeding
- Regular use of dietary supplements (see §6.8 Concomitant Therapy)
- Use of (chronic) medication (see §6.8 Concomitant Therapy)

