## 6.8 Concomitant Therapy

Participants may not use dietary supplements and/or chronic medication.

Participation is possible if the intake of dietary supplements is stopped at least 10 days before the screening visit and throughout the study duration.

For chronic medication use, an individual assessment will determine whether the medication could affect the study endpoints or whether taking the study product is contraindicated.

For example, participation is possible for individuals using antihypertensive drugs if the dosage is stable and will not change during the study. The participant must still meet the inclusion criterion.

Individuals who have been using, for example, a PPI for several months may also participate.

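### Eligibility sets a floor for systolic pressure but no ceiling for systolic or diastolic pressure, and the week-4 reading has no escalation level

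*Protocol*

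**What the plan says.** - **Population.** Protocol section 5.1 studies the product "in individuals with elevated systolic blood pressure", defined as 130 mmHg or more. The only inclusion criterion, in section 5.3, is "An average systolic blood pressure" at or above the same value.
- **Exclusions.** Section 5.4 opens with "Individuals meeting any of the following criteria will be excluded from participation in this study" and lists ten lines. None concerns a level of blood pressure.
- **Consequence of eligibility.** Section 4.1 states: "If eligible, the participant will be randomised". It adds: "Intake of the study product must start no later than 1 week after the screening visit".
- **Antihypertensive drugs.** Under section 6.8, "participation is possible for individuals using antihypertensive drugs if the dosage is stable and will not change during the study", provided the 130 mmHg floor is still met.
- **Readings.** Pressure is measured at screening, at week 4 and at the final visit. For week 4, section 8.1.2 asks only that the result be entered in the file, and it refers to a separate blood pressure measurement protocol.
- **Stopping.** Section 7.1 leaves stopping to the wish of the participant or the investigator. Section 7.1.1 adds: "The treatment will be stopped if the participant meets any exclusion criteria during the study". Section 7.1.2 adds: "Stopping the treatment will result in exclusion from the study".

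**The concern.** Blood pressure defines both the population and the primary endpoint, yet it is bounded on one side only. Someone whose screening average is very high meets the inclusion criterion and no exclusion based on pressure. Following the rule to the letter therefore leads to randomisation, with an even chance of placebo. At week 4 the text does not say who looks at the reading, or at what level anyone must act.

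The stake is the safety of a participant with severe hypertension during the study. Rules on who may enter, and on when a reading must be acted on, belong in the protocol and would not normally be left to a statistical analysis plan.

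**Working it through.** No statistical formula applies. The check sets the sections side by side and adds up the visit intervals.

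**1. Pressure limits in the text**
- Inclusion (5.1, 5.3): one limit, systolic average of at least 130 mmHg. Upper limits: 0. Diastolic limits: 0.
- Exclusion (5.4): 10 lines. Three carry a number (age, triglycerides, alcohol). Lines naming a pressure: 0.
- Discontinuation (7.1 to 7.1.2), week-4 visit (8.1.2) and safety reporting (8.5): pressure levels that trigger action: 0.

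**2. Does other text close the gap?**
- Section 5.2 rules out exemptions for people who do not meet the criteria. That bars people below the floor; it does nothing about people far above it.
- Section 5.4 excludes chronic illness, but section 6.8 admits users of antihypertensive drugs on a fixed dose, so hypertension as such is not excluded.
- Section 8.5.1 counts abnormal signs as adverse events, and events that the investigators judge a significant hazard as serious. A very high reading could qualify and then reach the medical monitor (8.5.3). Section 8.5.2 starts this collection at first intake, so the screening reading, which decides entry, falls outside it.

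**3. Time between scheduled readings** (inputs from 4.1: intake starts within 1 week of screening; interim reading 4 weeks after the start; final visit 8 to 9 weeks after the start)
- Total: at most 1 + 9 = 10 weeks, which reproduces the maximum stated in section 4.1.
- Screening to interim reading: at most 1 + 4 = 5 weeks.
- Interim reading to final visit: 8 − 4 = 4 to 9 − 4 = 5 weeks.
- Screening to start of adverse event collection: at most 1 week.

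**4. What a carelessly worded ceiling would do**

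A plain new line in section 5.4 would become a mandatory stop at week 4 through section 7.1.1, and an exclusion from the study through section 7.1.2. Participants would be removed according to the primary outcome variable, and more of them from placebo if the product works. Each one would be 1/28 = 3.6% of an arm and would use one of the 28 − 25 = 3 spare participants per arm (section 9.2). This is a cost of a bad fix and not of the present text, but it determines how the fix must be worded.

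**The case against.** The strongest reply is that the protocol does protect such participants, only without a number.

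- The investigator completes an inclusion checklist, and section 4.1 places randomisation 1 to 2 days after screening, when all results are in. A review step therefore precedes assignment.
- Section 6.8 requires an individual assessment of chronic medication.
- Participants are to receive their blood pressure values (2.2), and the identity link is kept so that information can be returned to them in their own interest (10.3).
- They may withdraw at any time (7.2), and some are recruited through their own physician (5.7).
- The measurement protocol and the checklist are not shown, and either could hold an alert value.

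Most of this stands, and it limits the consequence. It does not supply a ceiling. The review step before randomisation applies the stated criteria, which a very high value satisfies. Section 2.2 does not say when values are given. Recruitment also runs through staff channels and press releases, so a treating physician is not assured.

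A reader might infer that participants are denied treatment. The documents do not support that. The unchanged dose in section 6.8 is a condition of taking part, and no section bars a physician from starting or changing a drug; the consequence within the trial is at most stopping the product and leaving the study. Nor do they support the inference that there are no safeguards at all.

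**Conclusion.** The point holds for the protocol text. Eligibility is bounded only from below, no pressure ceiling appears in section 5.4, and section 8.1.2 does not escalate the week-4 reading. The stated rule admits a candidate with severely raised pressure to 8 to 9 weeks of supplement or placebo, with up to 5 weeks between consecutive scheduled readings.

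It is a low-ranking safety improvement, held with medium confidence. Two limits apply. The number of such participants cannot be derived from the documents, and an alert value may already exist in the measurement protocol or the checklist.

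A reader might also infer that very high baseline values would weaken the power or bias the comparison. That is not claimed: nothing in the documents gives the baseline distribution from which such an effect could be worked out.

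**What to change.** - **Section 5.4:** add an upper systolic and diastolic limit, at a value set by the principal investigator – medical monitor, applied to the average of the screening readings before randomisation. State that it applies at screening only, so that section 7.1.1 does not turn it into an automatic, outcome-dependent stop.
- **Section 8.1.2:** add one sentence that a week-4 reading above that level is passed promptly to the medical monitor, who decides on referral.
- **Alternative:** if the blood pressure measurement protocol already holds such a value, refer to it in sections 5.4 and 8.1.2 instead.

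The cost is one exclusion line, one checklist item and one sentence. No visit or measurement is added, because the screening readings are already taken in triplicate (8.1.1). The downside is that a few candidates with very high pressure are not enrolled and, under section 5.6, cannot be screened again.
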